### 5.4. STUDY METHODOLOGY

#### 5.4.1. *Measurements (performed at baseline, 3 and 6 months)*

##### **a. Breast size**

Breast development will be assessed by measuring chest and breast circumference to allow calculation of estimated cup size and to allow comparison with other studies . (16) Chest photography will be used to calculate estimated breast volume using the BreastIdea Volume Estimator application using 2D images (24), and 3D imaging using a Microsoft Kinect camera and freely available KScan3D software (version 1.2.02, LMI Technologies, Canada). Photography images will include the area from the top of the shoulders to the bottom of the breast and will not include the face nor any identifying information. Photography images will only be labelled with participant study ID, UR number and date. Patient satisfaction will also be measured using a 5 point Likert-type Scale.

##### **b. Serum Total Testosterone by LC-MS**

T levels in the vast majority of studies cited here were measured by immunoassay, which are notoriously inaccurate for quantifying low levels of circulating T (i.e. female range). Comprehensive studies of all available commercial T immunoassays show major method-dependent discrepancies between immunoassays which all deviate from mass-spectrometry (MS)-based methods (25). Newer LC-MS equipment has overcome the previous limitations of

MS technology by providing greatly enhanced sensitivity while retaining reference level specificity. (26) Therefore, LC-MS via a validated NATA accredited laboratory will be used to ensure accurate and robust T results for the study. Serum T will be measured early morning in the fasting state. For E2 valerate titration, serum E2 will be determined using a clinical electrochemiluminescence immunoassay assay (Cobas C8000, Roche Diagnostics). E2 assay has an inter-assay variation of 3.5% at 330 pmol/L and 1.9% at 1800 pmol/L and will be measured at each time point to allow for adjustment of E2 valerate dose as per clinical guidelines.

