### 5.3. RANDOMISATION

Participants will be individually randomised by a third party to intervention group 1 (cyproterone acetate 12.5mg daily) or intervention group 2 (spironolactone 100mg daily) in a 1:1 ratio according to a computer generated randomisation procedure, stratified in blocks for baseline age (< 27 and > 27 year-old) and BMI (<24.7 > 24.7 kg/m^2), with cut-offs corresponding to medians found in our previous studies of these individuals. A block size of 2 is chosen, with intervention group allocation randomly permuted and balanced within blocks. Low dose cyproterone 12.5mg has been chosen as this is effective, and reports of meningioma have occurred with higher doses >25mg daily (22). Austin Health Pharmacy Clinical Trials Team will prepare spironolactone 100mg or cyproterone acetate 12.5mg in matching identical capsules. All participants will receive standard care, which will include E2 valerate 4mg daily or equivalent transdermal E2 as an initial dose as per current guidelines (23). A nocte dose will be used so that early morning fasting blood tests will reflect peak serum E2 levels. As per standard clinical care, the E2 valerate dose will be monitored monthly in the first 3 months to ensure serum E2 levels remain in the target range of 250–600 pmol/L (23). The dose will be increased by 2mg each month if levels are below the target range.

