## 9. STORAGE OF BLOOD AND TISSUE SAMPLES

### 9.1. DETAILS OF WHERE SAMPLES WILL BE STORED, AND THE TYPE OF CONSENT FOR FUTURE USE OF SAMPLES

All routine laboratory studies aside from the sex steroid analyses will be performed at Austin Pathology. The results of these tests will go into the participant's Austin Health medical record and be collected separately in their study file. Blood will be discarded within 14 days.

Blood for sex steroid analysis will be collected and couriered to Monash Pathology for analysis via MS/LC-MS. The results of these tests will go into the participant's Austin Health medical record and be collected separately in their study file. The serum estradiol levels will be used for titration of estradiol therapy. Blood samples will be discarded by Monash Pathology within 14 days of analysis.

In collaboration with MCRI, an aliquot of de-identified blood from trial participants will be transferred to MCRI for epigenetic analysis. Blood samples will be discarded within 14 days of analysis.

With additional consent, participants may have their blood stored for future research and genetic testing. The frozen aliquots will be maintained in a locked Austin Health Endocrine Department Laboratory freezer at -80 degrees Celsius indefinitely. These samples will only be labeled with study number and unit record number. Specimen storage will be the responsibility of the PI.

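### Sections 5.4.1b and 9.1 disagree on which assay supplies the estradiol value used for titration, and 9.1 files sex-steroid results, testosterone included, unmasked in the hospital record of a double-blind trial

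*Protocol*

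**What the plan says.** **Assay, section 5.4.1b.** For titration, "serum E2 will be determined using a clinical electrochemiluminescence immunoassay assay". The section names the platform, quotes its inter-assay variation, and says estradiol "will be measured at each time point to allow for adjustment of E2 valerate dose as per clinical guidelines". It does not name the laboratory that runs this assay.

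**Assay, section 9.1.** The hospital laboratory is given everything except sex steroids: "All routine laboratory studies aside from the sex steroid analyses will be performed at Austin Pathology". Then: "Blood for sex steroid analysis will be collected and couriered to Monash Pathology for analysis via MS/LC-MS". The same paragraph goes on: "The results of these tests will go into the participant's Austin Health medical record and be collected separately in their study file", and directly after that: "The serum estradiol levels will be used for titration of estradiol therapy".

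**Use of the value, section 5.3.** The estradiol dose is monitored monthly in the first 3 months "to ensure serum E2 levels remain in the target range of 250–600 pmol/L", and a level below that range triggers a dose step.

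**Blinding.** The synopsis and section 5.1 describe the trial as double-blind. Section 7.1 considers whether hyperkalaemia could affect blinding and concludes that it should not. No section discusses testosterone results in this respect.

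**The concern.** There are two separate issues.

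First, estradiol is background treatment in both arms. By the protocol's own account (section 3.3) it lowers testosterone and is accompanied by breast development, so it bears on the primary endpoint and on the first secondary endpoint. One fixed range governs its dose. The protocol should therefore be clear about which measurement is compared with that range, and its two statements point to different methods.

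Second, the comparison is between two drugs that the protocol expects to differ strongly in testosterone suppression. An on-treatment testosterone result is therefore informative about allocation. Section 9.1 routes it into a record that clinical staff ordinarily use, with no instruction to withhold it. At stake is the blind for whatever is assessed after the result is filed. At month 6 that includes breast imaging, the PHQ-9 and the GPSQ.

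**Working it through.** **1. The two sections side by side**

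| | Section 5.4.1b | Section 9.1 |
|---|---|---|
| Purpose | Estradiol for titration | Estradiol for titration |
| Method | Electrochemiluminescence immunoassay | MS/LC-MS, the only method in the paragraph |
| Laboratory | Not named | Outside laboratory, as opposed to the hospital's own |
| Where results go | Not stated | Medical record and study file |

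Section 9.1 does not say in so many words that estradiol is measured by MS/LC-MS. It follows because estradiol is a sex steroid, sex steroids are carved out of the hospital laboratory's work, the paragraph gives no other method, and the titration sentence stands in it. No sentence says which result governs if both exist.

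**2. Can the effect on dose steps be sized?** That needs the proportional difference between the two assays for estradiol and the distribution of estradiol around 250 pmol/L. The protocol gives neither. The quoted inter-assay variation (3.5% at 330 pmol/L) describes the immunoassay's own imprecision, not its difference from mass spectrometry. The statement in 5.4.1b that immunoassays deviate from mass spectrometry concerns testosterone. So no figure is given here.

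**3. When could on-treatment testosterone be seen?**
- Section 5.4.1, which contains the testosterone measurement, is headed for baseline, 3 and 6 months.
- The testosterone endpoint (section 4.3) is at 3 and 6 months.
- Section 5.4.2 gives the purpose of the month 1 and 2 blood tests as monitoring the estradiol dose.

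On-treatment testosterone is therefore specified at months 3 and 6 only. Within the monthly titration period the overlap is month 3. That result precedes the month 6 assessments.

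**4. How informative is one result?** Inputs: 1:1 allocation (section 5.3); below 2 nmol/L in 90% on cyproterone (sections 3.2 and 8.1); in 48% (section 8.1) or 40% (section 3.2) on spironolactone.

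As a check on these inputs, section 8.1 uses 48% against 90% to reach 25 per group at power 0.9 and level 0.05. The pooled two-sided formula, with mean proportion 0.69, gives

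n = [1.960 × √(2 × 0.69 × 0.31) + 1.282 × √(0.48 × 0.52 + 0.90 × 0.10)]² / 0.42² = 23.3, so 24 per group.

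This is close to the stated 25. With 20% dropout, 50 / 0.8 = 62.5, so 63 against the stated 64. Nothing in this point changes the sample size.

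With equal allocation, Bayes' rule gives:

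| | Spironolactone 48% | Spironolactone 40% |
|---|---|---|
| P(cyproterone given T < 2) | 0.90 / (0.90 + 0.48) = 0.65 | 0.90 / (0.90 + 0.40) = 0.69 |
| P(spironolactone given T ≥ 2) | 0.52 / (0.52 + 0.10) = 0.84 | 0.60 / (0.60 + 0.10) = 0.86 |
| Correct guess overall | 0.5 × (0.90 + 0.52) = 0.71 | 0.5 × (0.90 + 0.60) = 0.75 |

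Chance is 0.50.

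**5. Does settling the assay settle the blind?** No. Section 9.1 sends sex-steroid results to the record in any case, and testosterone is among them. If titration estradiol came from the immunoassay, testosterone would still be filed there.

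**The case against.** The strongest reply is that 5.4.1b is the methods section and is specific, while 9.1 concerns storage and disposal and may simply be loosely worded. One laboratory could run testosterone by LC-MS and estradiol by immunoassay. This is fair, and it means the conflict may be one of wording only. It does not remove it, because 9.1 addresses the same value for the same purpose and a reader following it would use a different method.

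A reader might go further and infer that a sizeable share of dose steps would go the other way. The documents do not support this. Neither section prescribes mixed use across participants or visits, and with one assay throughout no such inconsistency arises. Nothing links assay to arm, so any added noise would not favour either drug. The size would rest wholly on outside assumptions.

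A reader might also infer that the titrating clinician sees testosterone at every monthly check, or that the 9.1 estradiol route is what exposes it. Neither holds: no testosterone result is specified at months 1 and 2, and the filing instruction, not the choice of estradiol assay, creates the exposure.

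Three further limits stand:
- The 90%, 48% and 40% rates come from the investigators' earlier data. The protocol describes these as a retrospective audit of people on estradiol for more than 6 months, with testosterone by immunoassay. They are not forecasts for month 3.
- The protocol does not say who titrates or who may open the record.
- The dose step depends on estradiol, not testosterone, and LC-MS testosterone is hard to influence. The exposure matters more for self-reported and observer-dependent measures.

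**Conclusion.** The point holds in two limited parts.

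- **Assay.** Sections 5.4.1b and 9.1, on their natural reading, give different methods for the estradiol value compared with 250–600 pmol/L. This is an inconsistency to reconcile. Its effect on dosing cannot be sized from the protocol, and no claim is made that it biases the comparison between arms.
- **Masking.** Section 9.1 puts on-treatment testosterone (months 3 and 6) in the hospital record with no provision to withhold it. One result at the 2 nmol/L cut-off would identify the arm about 71% to 75% of the time, against 50% by chance. This assumes that the protocol's indicative rates apply and that blinded staff read the record, which is likely if estradiol is looked up there but is not stated.

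Sample size and power are unaffected. The case for acting rests on how little the correction costs relative to protecting the blind, not on a demonstrated bias.

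**What to change.** 1. Reconcile 5.4.1b and 9.1 so that one named assay and one named laboratory supply the titration estradiol for all participants at all visits. Either can be kept as far as this point goes.
2. Amend 9.1 so that the estradiol result is released to the titrating clinician on its own. Keep on-treatment trial testosterone out of the accessible record, and withhold it from blinded staff and participants until database lock. Baseline testosterone, which eligibility requires, is not affected.
3. State in the protocol who titrates and who may see sex-steroid results during the trial.

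The cost is amendment wording and a reporting instruction to the laboratory. The drawback is that estradiol and testosterone must be reported separately. The target range and the dose steps are not at issue and need no change for this point.

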### **c. Immune-profiling, Epigenetics & Sexual dimorphism**

We will refer deidentified blood samples to the Trained Immunity Epigenetics Team at the Murdoch Children's Research Institute (MCRI) for immune-phenotyping, and epigenetic and transcriptomic profiling of specific innate (monocytes) and adaptive (naïve T and B) cell types. This will evaluate the changes in immune function during sex hormone administration. This is important given that risk of infection is different in genetic males and genetic females, but it is unclear whether this is related to sex hormone concentrations or underlying genetics. Specifically, a participant's leukocytes will be isolated from the buffy coat of a 6mL blood sample and sorted using multi-colour flow cytometry to measure circulating blood cell populations, and cells will be sorted for epigenomic analysis, including: genome-wide DNA methylation (EPIC array), RNA expression (RNA-seq) and histone modification (ChIP-seq). Results of these analyses have no implications for the participant or their family's health or wellbeing.

### **d. Body Composition by DXA**

Body composition to determine regional fat distribution (percentage android, leg and gynoid fat mass, and total fat mass) will be determined by DXA (Prodigy Version 7.51 GE Lunar, Madison, WI) (27).

### **5.4.2 Safety assessments and withdrawal (performed at baseline, 1,2,3, and 6 months)**

Questionnaires to monitor for depression (PHQ-9) and gender dysphoria (GPSQ)(21) will be used. Blood pressure, medical conditions and medication use will be recorded each visit. Serum urea, electrolytes and creatinine will be monitored to assess for risk of hyperkalaemia, dehydration or renal impairment which may occur with spironolactone. An ECG will be performed at baseline and 6 months to monitor the QTc, prolongation of which has been associated with androgen deprivation therapy in men with prostate cancer. (28) Adverse events will be actioned as per Ethics Committee guidelines. Participants will be withdrawn if they meet the criteria for exclusion, or have a change in safety assessments that necessitate

clinical intervention. A further blood test at months 1 and 2 will be obtained to monitor the E2 valerate dose to ensure serum E2 remain in the target range.

## **6. STUDY POPULATION**

### **6.1. RECRUITMENT PROCEDURE**

Given the lack of research, the transgender community are a highly enthusiastic cohort, welcoming of well-designed research studies as we observed during 2017. For this study, we will recruit transgender individuals attending our endocrine clinics. Together with Equinox Gender Clinic (a GP clinic specialising in transgender health), as of December 2016, we have an established database of over 540 individuals regularly attending our clinics. Numbers of new presentations are rapidly increasing each year. Furthermore, close collaborations with the largest GP clinics that specialise in transgender health, namely Equinox Clinic, Northside Clinic and Prahran Market Clinic, as well as the Royal Children's Hospital in Melbourne, have enabled us to recruit 48 individuals newly commencing cross-sex hormone therapy in the last 8 months (6 per month). Based on the trajectory of new presentations attending our clinic, we expect this number to double over the next 2 years. Through active community engagement, we have also recruited 964 transgender adults across Australia to participate in an online transgender health survey.

### **6.2. INCLUSION CRITERIA**

1. Male-to-female individuals diagnosed with gender dysphoria according to the DSM-V criteria who are about to commence treatment with anti-androgen therapy, are on E2 and their baseline total testosterone > 10nmol/L (in the male reference range).
2. Aged from 16 – 80 years (individuals with gender dysphoria choosing to access CHT can do so after the age of 16 without requiring parental consent).

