| Hospital:                   | Austin Health                                                                                                                                                                                                                                                                                                                                                                                                  |
| Study Question:             | Is cyproterone acetate more effective than spironolactone in lowering endogenous testosterone levels and increasing breast volume and feminine fat distribution in male-to-female individuals commencing estradiol therapy?                                                                                                                                                                                    |
| Study Objectives:           | 1. To compare the effectiveness of cyproterone acetate and spironolactone as an anti-androgen agent in male-to-female transgender individuals commencing estradiol.                                                                                                                                                                                                                                            |
| Primary Endpoint:           | Breast volume                                                                                                                                                                                                                                                                                                                                                                                                  |
| Secondary Endpoint:         | 
 
1. Percentage of individuals who have total testosterone levels <2 nmol/L (in the female reference range) at 3 and 6 months.
 
2. Fat mass including leg and gynoid regional fat;
 
3. Depression assessment using Patient Health Questionnaire 9;
 
4. Gender Dysphoria using the Gender Preoccupation and Stability Questionnaire.
 
 |

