| Inclusion Criteria:         | 
 
1. Male-female individuals aged 16-80 years
 
2. About to commence treatment with feminising hormone therapy with anti-androgens
 
                                                                                                                                                                                                                      |
| Exclusion Criteria:         | 
 
1. Evidence of androgen deficiency at baseline (T<10nmol/L)
 
2. Any contraindications to spironolactone, cyproterone acetate or E2 therapy
 
                                                                                                                                                                                                        |
| Number of Planned Subjects: | 64                                                                                                                                                                                                                                                                                                                                                                                                             |
| Safety considerations:      | 
Regular monitoring for adverse physiological and psychological effects during routine care of cross-sex hormone therapy, including:
 
 
1. Monitoring of E2 levels
 
2. Monitoring for changes in depression and gender dysphoria
 
                                                                                                                  |

|                      |                                                                                                                                                             |
|----------------------|-------------------------------------------------------------------------------------------------------------------------------------------------------------|
|                      | Ensuring safety when obtaining blood tests.                                                                                                                 |
| Statistical Methods: | Generalised linear mixed model with a restricted maximum likelihood function to determine between group differences in the main outcome measures over time. |

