Preliminary data from our retrospective audit (5) of 540 individuals (n=80 male-to-female on E2 for >6 months) suggest that on univariate and multivariable analyses, the cyproterone acetate group had significantly lower total T levels (overall  $p<0.0002$ ) than the spironolactone group and the E2 alone group. **Ninety per-cent** of the cyproterone acetate group and 40% of the spironolactone group had total T levels < 2 nmol/L. This preliminary study also found that serum urea level was higher (5.2 vs 4.4 mmol/L,  $p=0.035$ ) in the spironolactone group. No differences were observed in total daily oral E2 valerate dose, E2 level achieved, blood pressure, creatinine, or liver function. Supporting our findings, a recently published US retrospective audit of 98 male-to-females found only a quarter of those on spironolactone achieved T in the female reference range (6). Given the limitations of retrospective cross-sectional studies with potential for bias associated with choice of anti-androgen treatment, and the fact that T was measured by immunoassay which lacks precision at low serum T concentrations (as opposed to more sensitive liquid chromatography-tandem mass spectrometry (LC-MS), a prospective randomised double-blind trial to evaluate the optimal anti-androgen agent is warranted.

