## **4. STUDY OBJECTIVES**

### **4.1. HYPOTHESIS**

In male-to-female individuals commencing estradiol therapy for feminisation, additional cyproterone acetate will be more effective than spironolactone in (a) increasing breast volume and feminine fat distribution (increasing gynoid and leg regional fat), and (b) lowering endogenous testosterone levels,

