## 5. STUDY DESIGN

### 5.1. STUDY TYPE & DESIGN & SCHEDULE

This is a double-blind, randomised trial in adults aged 16-80 years to compare the anti-androgen effects of 6 months of cyproterone acetate versus spironolactone in 64 male-to-female transgender individuals on E2 therapy. This is a single site study.

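### Inclusion criterion 1 (Protocol 6.2) requires people already on estradiol, while the study question, objective and hypothesis concern people starting it

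*Protocol*

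**What the plan says.** The eligibility rule is inclusion criterion 1 in Protocol 6.2: participants are those "who are about to commence treatment with anti-androgen therapy, are on E2 and their baseline total testosterone > 10nmol/L". The sentence treats the two drugs differently. The anti-androgen is still to come, and E2 is already being taken. Exclusion criterion 1 in 6.3 repeats the testosterone threshold from the other side. Neither 6.2 nor 6.3 sets a maximum duration or dose for prior E2, or a washout.

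The statements of purpose describe a different person. The study question in the synopsis asks about "feminine fat distribution in male-to-female individuals commencing estradiol therapy", and the objective beneath it uses the same population. The hypothesis in 4.1 reads "In male-to-female individuals commencing estradiol therapy for feminisation, additional cyproterone acetate will be more effective than spironolactone".

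Section 5.3 gives all participants "E2 valerate 4mg daily or equivalent transdermal E2 as an initial dose as per current guidelines", checks the dose monthly for 3 months, and raises it by 2 mg a month when E2 is below target.

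**The concern.** Eligibility wording decides who is enrolled and to whom the result applies. For a person who has never taken E2, the study question says this is the trial's subject, while 6.2 says they do not yet qualify. Screening staff cannot follow both.

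The opposite case also matters. Someone who has taken E2 alone for a long time and now wants to add an anti-androgen can satisfy 6.2. For that person the starting dose in 5.3 has no clear meaning: either the current dose is reset to 4 mg or the protocol is not followed.

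The endpoint makes the timing relevant. Breast volume is primary, and the tables in 5.1 and 5.2 place chest photography at 0 and 6 months. Section 3.3 cites a European observational study in which growth was concentrated in the first half-year of feminising hormone therapy. If E2 began well before visit 1, part of that growth could already be present in the baseline image and so fall outside the interval the trial observes.

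**Working it through.** This is a comparison of texts. The only figure to check is the sample size, to see whether the point touches it.

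**Sample size (8.1).** Inputs: 48% against 90% with T below 2 nmol/L, power 0.9, significance level 0.05, taken here as two-sided because the protocol does not say. Per group, n = [1.96·√(2·p̄·(1−p̄)) + 1.2816·√(p₁(1−p₁) + p₂(1−p₂))]² / (p₁−p₂)².
- p̄ = (0.48 + 0.90)/2 = 0.69, so the first term is 1.96·√0.4278 = 1.282.
- The second term is 1.2816·√(0.2496 + 0.09) = 0.747.
- n = (2.029)²/(0.42)² = 23.3, rounded up to 24, against the stated 25. Power at 25 per group is 0.920.
- With 20% dropout, 25/0.8 = 31.25, rounded up to 32 per arm, or 64 in all.

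The stated figure reproduces to within one per group. It rests on testosterone suppression and contains no term for breast volume or prior E2, so the point leaves it unchanged. Section 8.1 says there are no preliminary data on breast size.

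**Who is described where.**
1. Synopsis study question and objective: starting E2, stated directly.
2. Hypothesis, 4.1: starting E2, stated directly.
3. Section 5.3, "E2 valerate 4mg daily or equivalent transdermal E2 as an initial dose as per current guidelines": a starting dose with titration. It is not an eligibility rule, but it fits new starters and does not fit established users.
4. Synopsis inclusion criterion 2, "About to commence treatment with feminising hormone therapy with anti-androgens": does not name E2 and does not require it. Indirect support only.
5. Recruitment, 6.1: the quoted rate of 6 per month is for people just starting hormones.
6. Inclusion criterion 1, 6.2: already on E2.

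**What 6.2 does when applied literally.**
- E2-naive, would start both drugs at visit 1: not eligible.
- Began E2 shortly before, T still above 10 nmol/L: eligible.
- On E2 for a long time, no anti-androgen, T still above 10 nmol/L: eligible, with no limit on duration.
- On E2 with T below 10 nmol/L: excluded.

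**Could the third group exist?** Section 3.2 describes an audit subset ("n=80 male-to-female on E2 for >6 months") in which the cyproterone group had lower T "than the spironolactone group and the E2 alone group". So some people stay on E2 alone beyond 6 months. The size of that group, and how many had T above 10 nmol/L, are not given.

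**The case against.** The strongest reply is that this is a drafting slip with little consequence. E2 begun shortly before the capsule would satisfy both 6.2 and the hypothesis, which itself speaks of cyproterone as additional treatment. The recruitment stream in 6.1 is new starters, and the testosterone threshold removes anyone in whom E2 has already suppressed T below 10 nmol/L. Much of this stands, and it rules out several stronger readings that a reader might infer.

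- *That 5.1 is also in conflict.* Its phrase "64 male-to-female transgender individuals on E2 therapy" reads naturally as background treatment during the 6 months, which is true of everyone under 5.3. It needs no change.
- *That 6.2 shuts out the target population altogether.* A new starter becomes eligible once E2 has begun, provided T is still above 10 nmol/L. The literal text bars a simultaneous start; it does not bar new starters for good.
- *That prior E2 is wholly unrestricted.* Section 3.3 says E2 lowers T to a degree, so the threshold limits prior effect indirectly. It does not limit duration, and 3.2 says E2 alone is usually not enough to lower T.
- *That the breast-volume contrast is diluted by a known amount.* The share of prior users and the growth they have left are not in the documents. The timing statement in 3.3 is about feminising hormone therapy, not specifically about E2 alone with T in the male range. Nothing says established users will be recruited.
- *That the analysis must adjust for prior E2.* Covariate choice can be left to an analysis plan that is not shown. The defect lies in the eligibility text.

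What the reply does not remove is that 6.2 is an operative rule that gives the wrong answer for an E2-naive person and no answer on how much prior E2 is acceptable.

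**Conclusion.** The point holds as an inconsistency in the eligibility rule. Section 6.2 conflicts directly with the study question, the objective and the hypothesis, and does not fit the dosing in 5.3. This rests on the current wording alone.

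The consequence is less certain. If people with substantial prior E2 enter, some of their growth may precede the baseline image, and the population to which the result applies becomes less clear. That depends on two things the documents do not settle: whether such people are enrolled, and whether E2 alone with T above 10 nmol/L produces appreciable early growth. No size can be given. Randomisation still protects the comparison between arms, and 25 per group and 64 in total stand as stated. The correction is worth making because it is cheap and concerns who is enrolled.

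**What to change.** Reword inclusion criterion 1 in 6.2 so that participants *are about to commence E2 and anti-androgen therapy*, keeping the T requirement. This brings it into line with the synopsis study question and objective, 4.1 and 5.3. If the investigators want to accept people who have already begun E2, state a short maximum duration in 6.2 and add a sentence to 5.3 on what happens to the current dose. In either case record the E2 start date at screening; 5.4.2 already records medication use at each visit, but does not name this date.

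The cost is one reworded criterion and one extra data item. The downside is possibly slightly slower recruitment, since long-term E2 users would no longer qualify.
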